### Health economic analyses

#### Perspective

The evaluation will primarily adopt a health and social care perspective as preferred by the National Institute for Health and Care Excellence (NICE) for decision-making, including both direct and indirect costs of low uptake and sub-optimal adherence. Other resources relevant to a wider societal perspective such as informal care and productivity loss (due to time off work) will be included in the secondary analyses.

Intervention costs will be estimated from information relating to staff time (RNs) in delivering the SUPA intervention, including time spent training and actually delivering the intervention, and other non-staff costs (e.g. manual development and printing). The frequency and duration of health and social care service use data will be combined with appropriate unit costs to generate total care costs per patient.

Costs will be compared between intervention and control groups. Bootstrapping methods will be used to produce confidence intervals around the cost differences to account for skewness often associated with the distribution of cost data. Costs will be combined with the primary trial outcome in the form of cost-effectiveness analyses. However, as the primary outcome is not a clinical outcome and is condition specific, quality adjusted life-years (QALYs) estimated from the EQ-5D will be used to estimate cost-effectiveness. The use of QALYs and the EQ-5D in HIV is supported by previous work. If the intervention results in reduced costs and better outcomes then it will be defined as being ‘dominant.’ However, supposing the costs are higher and outcomes are better, then incremental cost-effectiveness ratios will be calculated to show the extra costs incurred to gain an extra level of outcome. Uncertainty around cost-effectiveness estimates will be explored using cost-effectiveness planes. The results will be further evaluated using cost-effectiveness acceptability curves.

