### Intervention: SUPA intervention + care as usual (CAU)

The SUPA intervention has been described in detail in a separate publication ([name], [name], [name], [name], [name], [name]: SUPA Group. The development of an intervention to support uptake and adherence to antiretroviral therapy in people living with HIV: the SUPA intervention, submitted). Patients randomised to the intervention group will receive treatment initiation support within 1 month of enrolment into the intervention trial. This support will be in the form of 4 tailored treatment support sessions delivered by a Research Nurse (RN) utilising a collaborative Cognitive Behavioural Therapy (CBT) and Motivational Interviewing (MI) approach. The sessions will be conducted face-to-face (or by telephone if the patient prefers or cannot meet face to face) and will communicate a rationale for the personal necessity of medication, elicit and address concerns about medication and problem-solve potential practical barriers to adherence. Sessions will be tailored to individual needs and preferences, based on (1) the individual patient’s perceptions and practical barriers to ART identified using the BMQ-ART, and (2) salient issues arising during the sessions. An animation series and intervention manual have been developed as tools to communicate a rationale for the personal necessity of ART and to illustrate concerns and potential solutions. The specific timing of the sessions will differ according to the patient’s specific needs and availability; however, the first two sessions will take place within 1 month of enrolment, and sessions 3 and 4 will provide additional support 3 and 6 months post randomisation. These appointments will be scheduled at the patient’s convenience.

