## Discussion

We have described the design of the Supporting Uptake and Adherence to ART (SUPA) trial, an observational cohort study with nested randomised controlled trial evaluating the effectiveness of a CBT-based intervention to increase uptake and adherence to ART by addressing perceptual and practical barriers.

The intervention is based on the Necessity Concerns Framework and aims to address both perceptual and practical barriers to adherence as recommended by NICE [20] and BHIVA guidelines [9]. The intervention has been developed according to published guidelines for the development of complex interventions [15] and builds on preparatory research with PLWH showing that uptake and adherence to ART is driven by patients’ perceptions of their personal necessity for ART and concerns about adverse effects [18, 19]. To our knowledge, this is the first study to provide support at the time of a treatment recommendation to PLWH who may be at risk of delaying uptake or developing issues with adherence. This study targets individuals who may be considered as being hard to reach, and who are not usually represented in randomised trials. The study design allows the examination of process variables and the mechanism by which the intervention exerts its effect. The cost effectiveness analysis will enable health-care service providers to make informed decisions about the value of the intervention.

While it was not possible to mask the allocation of participants to intervention or control groups, we have taken steps to reduce bias, including blinding of the statistical team to group allocation and ensuring that data is not collected or entered by those delivering the intervention. It possible that the primary outcome measure (MEMS) may impact on adherence as it serves as a reminder to participants that they are monitored. However, the impact of adherence monitoring alone is likely to be minimal [36]. Although participants are selected for risk of delay to initiate treatment and nonadherence using a screening tool (BMQ-ART), patients who decline to take part in the study may represent a different group who are more at risk of disengaging from care. However, these participants will be followed up in the observational cohort, therefore their virological outcomes can be compared with those of trial participants.

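### The SUPA intervention cost includes manual development, a one-off cost already incurred, alongside recurring delivery costs, and so moves the economic result against SUPA by an unstated amount

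*Protocol article*

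**What the plan says.** The Perspective section builds the intervention cost from two groups of items. The first is research nurse time, "including time spent training and actually delivering the intervention". The second is "other non-staff costs (e.g. manual development and printing". The items are given as examples, and the section does not separate recurring from one-off items.

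The intervention section reports the materials as finished: "An animation series and intervention manual have been developed as tools". The Methods part of the abstract says the same.

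On purpose, the Perspective section states: "The evaluation will primarily adopt a health and social care perspective as preferred by the National Institute for Health and Care Excellence (NICE) for decision-making". The Discussion adds: "The cost effectiveness analysis will enable health-care service providers to make informed decisions about the value of the intervention".

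On the decision rule, lower costs with better outcomes count as dominance. Otherwise, "supposing the costs are higher and outcomes are better, then incremental cost-effectiveness ratios will be calculated". Cost differences get bootstrap intervals, and uncertainty is shown on cost-effectiveness planes and acceptability curves.

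**The concern.** A provider deciding whether to offer SUPA needs to know what providing it costs. Nurse time, training and printing arise again wherever it is delivered. The writing of the manual was complete before the article appeared, and no later decision about provision can undo that spending. Adding the two kinds of cost together gives a cost per patient that depends partly on how many patients the one-off item is divided among, and only partly on delivery.

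Three features of this plan make the mixture worth resolving:

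- The section on long-term cost-effectiveness expects QALY gains to fall mostly after the study period. The in-trial QALY difference, which is the denominator of the ICER, may therefore be small, and a fixed addition to the numerator is magnified.
- A charge that is equal for every SUPA patient moves the whole bootstrap interval for the cost difference without widening it. The reported uncertainty would not show that it is there.
- Dominance requires lower costs. A small saving on recurring costs could become a net cost through the one-off item alone.

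**Working it through.** **The plan's own figure.** The article states no intervention cost, development cost or ICER. The one reproducible figure that bears on a per-patient denominator is the sample size. For 45% against 60%, two-sided alpha 0.05 and 80% power:

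- Uncorrected: n = [1.960 × √(2 × 0.525 × 0.475) + 0.842 × √(0.45 × 0.55 + 0.60 × 0.40)]² / 0.15² = 172.8, rounded up to 173 per arm.
- With continuity correction: (172.8 / 4) × [1 + √(1 + 4 / (172.8 × 0.15))]² = 185.9, rounded up to 186 per arm, or 372 in total.

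This matches Table 1. The other four rows also reproduce with the correction (183, 183, 165, 134). With 1:1 allocation, 186 patients are planned for SUPA.

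**Direction.** Let D be the development cost and m the number of patients it is spread over. Control patients carry none of it.

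- Shift in incremental cost per SUPA patient = D / m, which is positive for any D > 0.
- Shift in ICER = (D / m) / ΔE, where ΔE is the gain in outcome. It is positive when ΔE > 0.
- Dominance is lost when the saving on recurring costs is smaller than D / m.

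**Size.** D, m and the QALY gain below are assumptions, except that m = 186 is the planned arm size. The 15-point gain is the difference used in the sample size section. The assumed QALY gain is 0.01.

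| Assumed D | D/186 per patient | per extra good adherer (÷ 0.15) | per QALY (÷ 0.01) | D/5,000 per patient | per QALY (÷ 0.01) |
|---|---|---|---|---|---|
| £1,000 | £5.38 | £36 | £538 | £0.20 | £20 |
| £10,000 | £53.76 | £358 | £5,376 | £2 | £200 |
| £50,000 | £268.82 | £1,792 | £26,882 | £10 | £1,000 |

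Worked line: £10,000 / 186 = £53.76; £53.76 / 0.15 = £358; £53.76 / 0.01 = £5,376.

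The QALY columns scale inversely with the assumed gain. At 0.05 QALY, £10,000 over 186 patients adds £1,075 per QALY; at 0.005 it adds £10,753. For dominance, £10,000 over 186 patients would turn any recurring saving below £53.76 per patient into a net cost. Over 5,000 users the threshold is £2.

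**The case against.** The strongest reply is that the article names a cost category and nothing more. It gives no amount and no denominator. Annuitising the cost, spreading it over expected users, or reporting results with and without it would all fit the sentence as written. A condensed article commonly leaves such detail to a fuller health-economics plan, which is not shown. Counting set-up costs, suitably spread, is also a defensible way to cost a complex intervention. Finally, the incremental cost is a difference in total care costs, including hospital care, tests and medication, so one item in one cost line may be small beside it.

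Much of this stands, and it rules out several stronger readings:

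- A reader might infer that the cost will be divided over the 186 trial patients. The article does not say so; 186 is only one end of the range shown above.
- A reader might infer that the ICER is shown to be biased. The direction follows from arithmetic, but the size cannot be derived, and an ICER is calculated only if costs are higher and outcomes better.
- A reader might infer that no adopting clinic would ever pay for materials. The article is silent on licensing, upkeep and adaptation, any of which could recur.
- A reader might infer that the evaluation as a whole would measure what the research cost. One component of the intervention cost does not do that.

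What the reply does not remove is the stated inclusion. The plan names manual development as part of the intervention cost without qualification, next to items that recur, in an analysis meant for provision decisions. The objection is to what is written, so an unseen document could only limit its effect.

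**Conclusion.** The point holds as a minor one. The plan puts a one-off cost already incurred into the SUPA intervention cost together with recurring items, which does not fit its purpose of informing provision. Any part of that cost charged to the SUPA arm raises the incremental cost by D/m. It therefore shifts the cost difference, a dominance finding, any ICER and the acceptability curve against SUPA.

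The size is unknown. Under the assumed ranges it runs from £0.20 per patient (£1,000 over 5,000 users) to about £269 (£50,000 over 186 patients). At an assumed 0.01 QALY that is £20 to £26,882 per QALY. It could be negligible or material, and the article does not allow a narrower statement. The point concerns the secondary objective on costs and has no bearing on the primary endpoint or the sample size.

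**What to change.** State in the health-economics plan that the main cost per patient and ICER use recurring costs only: nurse training and delivery time, printing, and any access to or upkeep of the materials. Report the development cost of the manual and the animation series as a separate line. Add one sensitivity analysis that includes it, spread over an explicitly stated number of expected users, and show the effect on the cost difference, dominance, the ICER and the acceptability curve.

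This takes a sentence or two and needs no new patient data. The Trial status section says that no analysis had been carried out when the article was submitted, so the rule could be fixed before results were known. The cost is one extra scenario to run and report.

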#### Determining the cost effectiveness of the long-term impact of the interventions

Although we will measure costs, QALYs and the cost per QALY over the study period, this information will be limited because it would be expected that QALY gains would largely occur later in time. To address this issue a Markov model will be constructed to examine how patients might move from one health state to another over a longer period of time. Health states will be defined according to CD4 counts or viral load. The probabilities of moving from one health state to another will be based on a review of the literature and from expert opinion. Assuming some degree of patient variation, the data collected in the trial will give information on EQ-5D utility scores and costs that are associated with different CD4 ranges and where necessary this information will be supplemented by data from the literature. As well as allowing us to assess the long-term cost-effectiveness of the interventions, this approach will enable an estimation of the long-term cost associated with different levels of ART uptake and adherence. This will be of importance from a public health perspective in that it will illustrate the economic savings that might be made through interventions. Increased uptake and adherence may have further benefits if infections in others are reduced and we will explore the possibility of incorporating such externalities into the model. The time horizon used will depend on data availability, but is it expected that we will measure costs and outcomes over a 5–10, and 15-year period. The results over the longer periods will by definition be more speculative.

### Internal feasibility review

Baseline data from the first 40 randomised patients (and 1-month data for those randomised to the intervention arm) will be reviewed with the Programme Management Group (PMG) and Programme Steering Committee (PSC) at respective group meetings. The groups will assess:Feasibility of recruitment and retention, identifying barriers to recruitment/retention and problems in delivery.Acceptability of study measures (Control and Intervention arms).Acceptability of the intervention by patients (Intervention arm only).Capacity of trial and local site personnel, including capacity of clinics to accommodate research staff, determining whether trial centres are fulfilling their commitments (i.e. helping with the identification and introduction of patients), and determining where further staff is needed to recruit patients and/or to deliver the intervention.

The findings of the feasibility review, along with participant feedback, will be used to make any necessary modifications to the conduct of the trial.

### Adverse events

Adverse events (AE) include any clinical change, disease or disorder experienced by the participant during their participation in the trial, whether or not considered related to participation in the trial. A Serious Adverse Event (SAE) will be defined according to usual clinical trial definitions. If the RA/RN is uncertain about whether the AE is an SAE, they will contact the centre Principal Investigator for their opinion. All SAEs must be reported by the RA/RN to the patient’s doctor (or doctor to the RA/RN), the centre Principal Investigator and the Trial Manager immediately. SAEs that are related to administration of any of the research procedures will be reported to the Sponsor and also sent to REC by the CI (or delegated individual) within 15 days of the CI becoming aware of the event.

After an SAE, a decision will be made as to whether the participant should be withdrawn from the trial, or need an alteration in their standard care. Arrangements will be made by the RN for further assessment and management as necessary. One month after an SAE, the RA/RN will provide both the site Principal Investigator and Trial Manager with a follow-up report. If the SAE is not resolved, further monthly reports will be sent via the Trial Manager to the Independent Data Monitoring Committee (IDMC). The RA/RN will forward these reports to the Research Ethics Committee, Sponsor, and local Research and Development (R&D) office.

### Trial discontinuation

If a member of the clinical care team or the RN feels that the intervention is detrimental (for example, causing distress), the patient can be referred out of the intervention. Referral to a more specialised professional should be carried out by the patient’s Clinician. Participants may discontinue from participation at any time, at the discretion of the Investigator. Specific reasons for discontinuing a participant from either study are:Withdrawal of informed consent.Development of exclusion criteria or other safety reasons during the study.Incorrect enrolment or randomisation of the participant.

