### Participants

#### Inclusion and exclusion criteria

Participant inclusion criteria (Phases 1 and 2): (1) patients aged 18 years or above; (2) diagnosed HIV infection; (3) no previous prescription of ART (except women who have previously been prescribed ART for prevention of transmission during pregnancy and subsequently discontinued, who are considered eligible); (4) clinical recommendation to initiate ART treatment according to contemporaneous British HIV Association (BHIVA) guidelines or as deemed appropriate by the patient’s clinician; (5) able to provide written informed consent and available for long-term follow-up. Participant exclusion criteria: (1) patients who do not speak English; (2) those who plan to leave the country in the next 12 months and hence will not be available for follow-up appointments or telephone follow-ups; (3) participants already enrolled in a trial or in any research study which encourages adherence (e.g. clinical trial of an investigational medical product); (4) lack of capacity to provide informed consent; (5) hospitalisation for a mental disorder in the past 2 years; (6) current suicidality or self-harm; (7) pervasive developmental disorder; (8) active substance misuse/dependence in last 3 months which in the opinion of the physician or investigator renders the patient unable to adhere to the study protocol; (9) patients who have previously started antiretroviral therapy and subsequently discontinued, except if they have previously taken ART for pregnancy; (10) psychiatric or addictive disorders which in the opinion of the clinician or investigator could preclude obtaining informed consent.

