### Primary endpoint

#### The proportion of months under follow-up where adherence is greater than or equal to 90%

Adherence is defined by MEMS data. As the distribution of this variable is unknown, we will categorise the proportion of participants achieving ≥90% adherence as < vs ≥0.8 of the follow-up months. Essentially, this study assesses whether the participant has been ≥90% adherent for at least 80% of their time spent in the trial. The 80% threshold to define a good outcome is based on the fact that 4–6 weeks delay to ART initiation following a treatment recommendation is reasonable, and if followed by consistent ≥90% adherence to ART for the remainder of the trial (10 of the 12 months), the participant is likely to achieve and maintain viral load suppression. To calculate each monthly adherence value, the percentage of adherence (according to MEMS) for each individual over each month of follow-up from randomisation will be calculated, treating every day off ART or not taking all prescribed ART doses (indicating either nonadherence or delayed treatment initiation) as 0% adherence.

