### Statistical methods and analysis

The SUPA intervention is hypothesised to be superior to care as usual, and therefore the planned analysis is intention to treat, including all randomised participants, with all participants analysed according to the study group to which they were randomised regardless of subsequent treatment received. Primary analysis will include all randomised participants other than those randomised in error (defined as not intending to randomise the participant through e.g. miscommunication, rather than a participant or clinician decision once the allocation has been given).

A per-protocol analysis will be carried out on the primary endpoint including all participants in the intervention group who attended all 4 (2 + 1 + 1) sessions. If the intention to treat and per-protocol analyses on the primary endpoint leads to inconsistent results, then per-protocol analysis will also be carried out on all the other endpoints.

Continuous variables will be summarised by medians and IQRs or means and standard deviations as appropriate depending on the distribution, and compared between groups using ranksum tests or t-tests respectively. Comparisons of change from baseline in continuous variables will adjust for any baseline imbalances using either quantile or normal linear regression (depending on the shape of the distribution).

Categorical variables will be summarised by frequency tables, and compared between groups using chi-squared tests, unless any cell count is < 5 or cell percentage is < 5% in which case exact tests will be used. Binary variables will be summarised by percentages, using standard exact 95% CI for the risk differences. Time-to-event variables will be summarised using Kaplan-Meier curves and average differences between randomised groups estimated using Cox models. Patients without the event recorded will be censored at their last clinic visit. Proportionality of hazards will be tested; where significant departures exist, varying differences between randomised groups over time will be estimated using flexible parametric models of Royston and Parmar. Rate of treatment switching will be analysed using Poisson regression, including all changes to ART as events and the total time under follow-up through the earliest of 12 months or the last patient visit as the person-time at risk. Primary analysis will not stratify by clinical centre.

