### Strategies to promote data completeness

We will take the following steps in order to promote participant retention and complete follow-up:Attempt to make the research visit convenient for participants by booking research visits to correspond with their regular care visits.Participants will be contacted by their preferred mode of contact ahead of their research appointments to remind them and confirm attendance.Participants will be offered the option of completing follow-up questionnaires by telephone.Contact details will be checked at each appointment.We will keep in touch with participants by sending a birthday card or text (provided the participant has consented to receive communication from us).

If the participant is withdrawn at the request of the Researcher or Clinician, final follow-up data should be collected as soon as possible (if appropriate). If the participant wishes to fully withdraw from Phase 1 or 2, the RA will contact the participant to ascertain the reason for withdrawal (although the patient does not have to give any reason), and ask whether they consent for previously collected data to be kept and analysed. The RA/RN will ensure that every effort is made to obtain any final follow up data (including MEMS caps). If the patient chooses to withdraw from attending the intervention only (not the trial), the RA should attempt to request permission to complete the further research follow-up visits (including keeping the MEMS caps) at the scheduled time points.

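### The discontinuation rule lets follow-up be cut short for reasons related to adherence, and the primary endpoint can then score a failure as a success

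*Protocol article*

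**What the plan says.** All references are to the protocol article.

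- **Trial discontinuation.** The general rule is "Participants may discontinue from participation at any time, at the discretion of the Investigator". A list follows, introduced by "Specific reasons for discontinuing a participant from either study are". It contains withdrawal of consent, "Development of exclusion criteria or other safety reasons during the study", and incorrect enrolment or randomisation.
- **Inclusion and exclusion criteria.** Exclusion 9 covers "patients who have previously started antiretroviral therapy and subsequently discontinued, except if they have previously taken ART for pregnancy". Exclusion 8 covers "active substance misuse/dependence in last 3 months which in the opinion of the physician or investigator renders the patient unable to adhere"; the adherence meant there is adherence to the protocol. Exclusions 5 and 6 concern recent psychiatric hospitalisation and current suicidality or self-harm.
- **Strategies to promote data completeness.** "If the participant is withdrawn at the request of the Researcher or Clinician, final follow-up data should be collected as soon as possible". The text limits this to cases where it is appropriate. Continued research visits and continued use of the MEMS cap are described only for a participant who leaves the sessions but stays in the trial.
- **Participants who delay starting ART (both arms).** Delaying or declining ART does not end participation.
- **Primary endpoint.** It is headed "The proportion of months under follow-up where adherence is greater than or equal to 90" per cent. Days off ART count as zero adherence. A good outcome is at least 0.8 of months, which the text explains as a share of the participant's time in the trial.
- **Statistical methods and analysis.** The analysis is by intention to treat, "with all participants analysed according to the study group to which they were randomised regardless of subsequent treatment received". The only exclusion is randomisation in error, narrowly defined.

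**The concern.** The entry criteria are reused as reasons to end participation, without saying which of them make sense after randomisation. New substance misuse, self-harm or psychiatric admission may well go with poor adherence, and exclusion 8 is itself partly a judgement about ability to adhere. Stopping ART, read literally under exclusion 9, is one of the failures the trial sets out to measure. The endpoint section counts such time as zero adherence, while the discontinuation section can be read as a reason to stop observing it.

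The result would be loss of follow-up that depends on the outcome. The trial is open-label and removal is discretionary, so its frequency could vary by site and by arm. Incorrect enrolment raises a related problem. An ineligible participant who was randomised intentionally stays in the analysis, but can lose the follow-up on which the analysis depends.

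**Working it through.** **1. The plan's own figure.** Table 1 gives 186 per arm for 45% vs 60% (80% power, two-sided alpha 0.05).

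- Pooled formula: n = [1.960·√(2·0.525·0.475) + 0.842·√(0.45·0.55 + 0.60·0.40)]² / 0.15² = 172.8.
- With continuity correction: (172.8/4)·[1 + √(1 + 4/(172.8·0.15))]² = 185.9, so 186 per arm and 372 in total.

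The other four rows reproduce in the same way. The sample size is not in dispute. It serves only as the base for step 4.

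**2. One participant.** Month 1 is non-adherent and months 2 to 6 are adherent. The participant stops ART at the end of month 6, is discontinued then, and stays off ART.

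- Months end at removal: 5/6 = 0.83, at or above 0.8, a good outcome.
- Followed to month 12, days off ART at zero: 5/12 = 0.42, a poor outcome.

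**3. When the classification flips.** Let d be the non-adherent months at the start and m the month at whose end ART stops and the participant is removed. A failure is scored as a success when (m − d)/m ≥ 0.8 and (m − d)/12 < 0.8.

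| Delay d | Removal months m that flip the result |
|---|---|
| 0 | any month up to 9 |
| 1 | 5 to 10 |
| 2 | 10 and 11 |

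The opposite error is also possible. A participant who is adherent throughout but removed at month 6 for another criterion scores 6/12 = 0.50 if unobserved months are counted as zero. Without continued data, neither scoring convention is safe.

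**4. Effect on the comparison.** The removal rates here are assumptions, since the documents give none. True success is 45% vs 60% with 186 per arm, and everyone removed is a true failure. "Missing" below divides the true proportion by the share remaining. "Flipped" adds the removed share to the successes, which is the extreme case.

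| Removed, control / intervention | Missing: observed success (difference) | Flipped: observed success (difference) |
|---|---|---|
| 10% / 10% | 0.45/0.90 = 50.0%, 0.60/0.90 = 66.7% (16.7) | 55%, 70% (15.0) |
| 10% / 5% | 0.45/0.90 = 50.0%, 0.60/0.95 = 63.2% (13.2) | 55%, 65% (10.0) |
| 15% / 5% | 0.45/0.85 = 52.9%, 0.60/0.95 = 63.2% (10.2) | 60%, 65% (5.0) |
| 5% / 10% | 0.45/0.95 = 47.4%, 0.60/0.90 = 66.7% (19.3) | 50%, 70% (20.0) |

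Power without continuity correction is 83% with no removals. At 10% / 5% it falls to 69% (missing) or 50% (flipped). At 15% / 5% it falls to 47% or 17%.

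**The case against.** Four stronger readings are tempting, and the documents do not support them.

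- **Removal is automatic.** It is not. The list sits under a sentence that leaves discontinuation to the investigator's discretion. Discretion does not remove the problem, however, because it lets practice differ between sites and arms.
- **The plan instructs sites to remove people who stop ART.** Exclusion 9 speaks of having previously started, which reads naturally as history at entry and mirrors the inclusion criterion on no previous ART prescription. Its pairing with safety reasons in the discontinuation list points the same way. The text is ambiguous, so the point rests more firmly on the substance misuse, suicidality and psychiatric criteria.
- **Intention to treat is broken.** The analysis section keeps every randomised participant except those randomised in error. The damage is to follow-up and scoring, not to the analysis set.
- **The treatment effect is overstated by a known amount.** No removal rate is given. Equal rates with flipped scoring leave the difference at 15 points, and unequal rates can move it either way.

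Two further objections have weight. The endpoint section also refers to months from randomisation and to 10 of 12 months, which fits a fixed 12-month denominator. On that reading truncated scoring does not arise, but the unobserved months still have to be filled. Also, both arms have research visits at 3, 6 and 12 months, so unequal detection through the intervention arm's sessions and 1-month visit is plausible but not shown.

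The plan does separate leaving the sessions from leaving the trial. It does not extend continued follow-up to participants discontinued by the researcher or clinician.

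**Conclusion.** The concern holds in limited form. The protocol permits investigators to end follow-up for reasons plausibly related to adherence, asks only for early final data when they do, and words the endpoint so that a failure can become a success (83% instead of 42% in the example). This sits badly with its own rules on delayed starters and days off ART.

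The individual misclassification depends on months ceasing to accrue at removal, a reading the text allows but does not compel. The effect on the between-arm difference depends on removal rates by arm, which the documents do not give, so neither its size nor its direction can be stated. The correction should be made because it is cheap and the loss it prevents is related to the outcome.

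**What to change.** Reconcile the sections on eligibility, delayed starters, the primary endpoint, analysis, discontinuation and data completeness. State that:

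1. the criteria on ART history apply at entry only;
2. a newly met exclusion criterion or incorrect enrolment does not by itself end outcome data collection, apart from the randomised-in-error cases already defined;
3. MEMS, pharmacy refill, viral load and clinic-record follow-up continue to 12 months from randomisation, unless consent is withdrawn or ethical or legal rules on loss of capacity prevent it;
4. the primary endpoint is scored over 12 months from randomisation for these participants.

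The rules for stopping the sessions or referring a participant out of them stay as they are.

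The cost is a protocol clarification to sites and some extra follow-up of participants who no longer attend sessions. The data sources are already in the plan. The trial status section reports participants still in follow-up and no cleaning or analysis begun when the article was submitted, so at that point the change could be made before any results were known.
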